### 9.3 Procedures at each visit

#### 9.3.1 Visit 1 – Screening.

After informed consent is obtained, the study staff will conduct vital signs and physical evaluation (including height and weight). The following procedures may be performed, data collected, and eligibility criteria checked and documented:

- Inclusion and exclusion criteria assessed.
- Demographics (year of birth, race/ethnicity, and gender).
- Diabetes and medical history (including severe hypoglycemia, DKA history, and microvascular complications).
- Substance use history (drinking, smoking, and drug habits).
- Prior and/or concomitant medications.
- Physical examination including weight, height, waist & hip circumference, waist-to-hip ratio, and vital signs (blood pressure, heart rate, and temperature).
- Electrocardiogram (ECG)
- Serum pregnancy test (serum beta-Hcg) for all females of child-bearing potential.
- Laboratory tests including Hb, hct, total serum bilirubin, direct bilirubin, indirect bilirubin, ALT, AST, ALP, PTT, PT, INR, GGT, serum albumin, pancreatic serum amylase, serum lipase, creatinine, eGFR (calculated by CKD-EPI), urine albumin/creatinine ratio (uCR), calcitonin, TSH, FT4, fasting plasma glucose (FPG) C-peptide (fasting), estradiol and FSH (if apply), TC, LDL, HDL, and triglycerides.
- HbA1c level measured using the DCA Vantage or similar point-of-care device/local lab.
- The study participant will receive a hypoglycemia diary to document clinically significant or severe (see **Annex 10** for hypoglycemia classification) hypoglycemia events, related symptoms, and precipitating activities such as meal omission, increased exercise frequency/intensity, or any other potential causes of hypoglycemia.
- AE/SAE assessment according to **Section. 10**.

Diabetes management information: We will record the participant's average total daily insulin use and total bolus insulin use (calculated over approximately two weeks), carbohydrate ratio, and correction factor (insulin sensitivity factor). Data from the participant's glucometer and CGM may be downloaded or recorded.

The participant will receive a study phone (if needed), an activity tracker (Fitbit sense 2), and the Dexcom G7 CGM system. The study apps (Fitbit app/SNAQ app) will be installed, and participants will receive training on their use. The study handbook also will be given to the participants.

If an exclusionary condition is identified, the study participant will be excluded from participation with follow-up and referral to their primary care physician as needed.

#### 2-Weeks Run-in Phase (baseline collection period)

This phase may begin immediately after enrollment is complete or be deferred for (maximum) 30 days if needed. This observational segment will collect data to compute baseline glycemic control metrics. Dietary history will be collected using the SNAQ app (for five days before the next on-site visit [V2]) to determine daily macronutrient consumption. The baseline data collection period will last for about two weeks up to 21 days after screening. Participants will be under their insulin-related standard of care treatment and wear their personal insulin pump and study-provided CGM. They will be asked to follow their usual care regimen with no restrictions. If needed, one or more interim visits or phone contacts may occur to assist the participant with any issues. Interim visit procedures will include the following:

- Assessment of compliance with the insulin-related standard of care treatment.
- Assessment of skin reaction in areas where a CGM sensor (and infusion set if applicable) was

worn.

- Assessment of eligibility to continue in the study.

To be eligible for randomization, participants must collect in at least 70% of the run-in phase time. If a participant fails to meet this criterion, or if it is determined that the participant will benefit from additional time with equipment use, the run-in period may be extended at the investigator's discretion. Additional visits and phone contacts for further training are at the investigator's discretion.

### 9.3.2 Visit 2 – Randomization.

Participants will be randomized 1:1 tirzepatide+AID or SoC+AID (**See Figure 1**).

#### Randomization arm A. Tirzepatide (*Mounjaro*®) +AID

We will dispense the study drug and start the titration phase of tirzepatide (*Mounjaro*®) for the intervention arm. A dose of 2.5 mg SC will be self-administered weekly for four weeks. The study participant will receive instructions on how to use the IMP (in the study handbook adapted for the intervention group) and the medication logbook for compliance check (**See section 8.4**). After four weeks of titration, the study drug will be up-titrated to 5.0 mg SC and kept for 16 weeks.

The study physician will configure the systems and pump parameters to mitigate the risk of hypoglycemia (**See Annex 2**). The study staff will review with the participants any possible parameter adjustments and frequency and how to identify when a parameter is being adjusted.

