| Measurements and procedures:           | 
The study consists of a screening, and eligibility assessment, followed by two weeks of baseline (run-in) period, randomization, four weeks of IMP up-titration, and 16 weeks of assessment as follows:
 
Visit 1 – Screening
 Visit 2 – Randomization
 Phone visit 1 – Escalation to target dose (intervention arm) and follow-up (control arm)
 Visits 3 – Outcomes evaluation
 Phone visit 2 - Outcomes evaluation
 Visit 4 - Outcomes evaluation (Last visit)
 Phone Visit 4 – Follow-up (intervention arm)
                                                                                                                                                                                                                                                                                                                                                                                                                                                                                                                                                                                                                                                                                                                                                                             |

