| Study Product / Intervention:          | 
Tirzepatide (Mounjaro®) is a clear, colorless to slightly yellow solution available in cartons containing four pre-filled single-dose pens or one single-dose vial: 2.5 mg, 5 mg, 7.5 mg, 10 mg, 12.5 mg, or 15 mg per 0.5 mL in a single-dose pen or vial.
 
In this study, we will start with the recommended starting dosage of tirzepatide (Mounjaro®): 2.5 mg injected subcutaneously once weekly (for four weeks). After four weeks, the dosage will be increased to 5 mg once weekly injected subcutaneously for 16 weeks.
                                                                                                                                                                                                                                                                                                                                                                                                                                                                                                                                                                                                                                                                                                                                                                     |

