### 3.5 Rationale for the dosage, route, and regimen

In this study, we will commence with the recommended initial dosage of tirzepatide (Mounjaro®), which is 2.5 mg administered subcutaneously once weekly for four weeks. The 2.5 mg dosage is for treatment initiation and is not intended for glycemic control (titration phase) (53).

After four weeks of dose escalation, the dosage will be increased to 5 mg once-weekly injected s.c. and kept stable for 12 weeks (treatment period). In case of intolerance to the medication, the dose can be scaled back. All participants will be encouraged to use a maximally tolerable dose of up to 5 mg/week (the lowest treatment dose of tirzepatide currently approved for T2D).

All patients will receive verbal and written education on using the tirzepatide (*Mounjaro®*) pen.

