6. STUDY DESIGN

6.1 General study design and justification of design

This randomized, parallel, open-label study evaluates the safety and efficacy of tirzepatide (*Mounjaro*®) 5mg as adjunctive therapy to AID in adults with T1D. The study consists of an eligibility assessment, screening, and randomization, followed by two weeks of a baseline (run-in) period, where participants will be requested to use their SoC+AID, wear a study activity tracker (Fitbit sense 2), and log meals using the SNAQ application (98). After baseline, participants in **Group A** will undergo an up-titration phase with 2.5 mg SC of tirzepatide once a week to assess drug-related tolerability. Participants in **Group B** will continue with their SoC+AID. After the four weeks of titration phase, participants assigned to Group A will hold stable adjunctive doses of tirzepatide (5 mg SC once a week) for up to 12 weeks. During the up-titration and assessment phases, participants will continue using the activity tracker and SNAQ app as instructed by the study team (**See Figure 1**). The primary and secondary outcomes will be assessed at 16 weeks of treatment and safety and exploratory endpoints will be evaluated at weeks 8, 12, and 16 (**See Chapter 5**).

[figure not shown]

Figure 1. Study Design.

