#### 9.2.2 Assessment of secondary (exploratory) outcomes

The secondary and exploratory outcomes will be assessed as follows:

The secondary outcomes based on CGM metrics and AID systems will be collected as described for the primary outcome and as repeated measurements from baseline to weeks 4, 8, and 16 of escalated treatment.

The anthropometric measurements and the record of the vital signs (blood pressure and heart rate, measured by pulse) will be performed according to the protocols for the World Health Organization's STEPwise approach to Surveillance (STEPS) (WHO 2017) (101). Height and body weight will be measured with *Seca Digital Ultrasonic Measuring Rod®* (Seca, Germany), with an accuracy of 0.1 kg. Waist circumference (WC) will be measured with a fiberglass anthropometric tape at the intermediate point between the lower edge of the last rib and the iliac crest in the horizontal plane (approximately 2.54 cm above the navel). The hip circumference will be measured around the widest part of the buttocks, making sure that the tape is snug but not tight, and is parallel to the floor. Body mass index (BMI) will be auto-calculated with the formula  $\text{weight}/(\text{height})^2$  in  $\text{kg}/\text{m}^2$ .

Vital sign measurements will be taken before obtaining an electrocardiogram (ECG) tracing and collecting blood samples for laboratory testing. The participant should sit quietly for five minutes before taking vital signs measurements. For each parameter, two measurements will be taken using the same arm, preferably the nondominant arm. The recordings should be taken at least one minute apart. Each pulse and blood pressure measurement will be performed sitting and recorded in the eCRF. Blood pressure will be taken with an automated blood pressure instrument.

Body composition: bioelectrical impedance analysis will assess global and regional fat mass (*Seca mBCA 514®*). For this study, fat mass percentage (FM%), fat mass index  $\text{kg}/\text{m}^2$  (FMI [total FM/height]), visceral adipose tissue liter ([I]VAT), lean mass index  $\text{kg}/\text{m}^2$  (LMI [total LM/height]) and appendicular lean mass index (ALMI [total LM/height]) will be considered relevant because they have been associated with an elevated risk of cardiometabolic diseases and mortality (102,103).

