#### Randomization arm B. Standard of Care+AID

Participants in arm B will continue with the SoC for diabetes management and AID during the titration and assessment period (16 weeks).

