bThe study includes a 4-week titration phase followed by 12 weeks at target doses, participants must use a non-oral highly effective method of contraception or add a barrier method for eight weeks (four weeks after IMP initiation plus four weeks after target dose escalation). After this period, participants may either return to their previous oral contraceptives (if they switched) or discontinue using a barrier method they were using concurrently.

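### The time at 5 mg is stated as 16 weeks in some sections and 12 weeks in others, so the tirzepatide course is 20 or 16 weeks, and the visit schedule fits only 16

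*Protocol*

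**What the plan says.** Three places describe a course of four weeks plus sixteen:

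- Synopsis, Study Product / Intervention: "After four weeks, the dosage will be increased to 5 mg once weekly injected subcutaneously for 16 weeks".
- Synopsis, Measurements and procedures: "four weeks of IMP up-titration, and 16 weeks of assessment as follows".
- Section 9.3.2, arm A: "After four weeks of titration, the study drug will be up-titrated to 5.0 mg SC and kept for 16 weeks".

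Three places describe four weeks plus twelve:

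- Section 3.5: "kept stable for 12 weeks (treatment period".
- Section 6.1: group A "will hold stable adjunctive doses of tirzepatide (5 mg SC once a week) for up to 12 weeks".
- Annex 7, Table A4 footnote b: "The study includes a 4-week titration phase followed by 12 weeks at target doses".

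Other parts of the protocol bear on the total. The arm B paragraph of Section 9.3.2, directly after the arm A text, has controls continue standard care "during the titration and assessment period (16 weeks". Chapter 5 and Section 9.2.1 compute the primary endpoint over the 12 weeks after dose escalation. Table 1 places the last drug dispensing at V3 (week 8), the return of unused pens and ketone meters at V4 (week 16), and a follow-up call for arm A at week 18 ±7 days. Section 9.3.6 heads V4 as the end of the intervention, and Section 9.3.7 puts the call about two weeks after treatment ends.

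On measurement times, Section 9.2.2 describes secondary CGM and pump outcomes "as repeated measurements from baseline to weeks 4, 8, and 16 of escalated treatment", while Sections 6.1 and 11.4.3 use weeks 8, 12 and 16.

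**The concern.** The length of the drug course is something staff and participants act on, and the two statements cannot both be followed. The longer one is not an isolated slip. It stands in the synopsis and in the Visit 2 procedure, the text in use when drug is first dispensed.

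Three things depend on the answer: the planned exposure, the number of doses behind the 75% compliance definition in Section 8.4, and whether the scheduled safety assessments cover the whole dosing period. Within Section 9.3.2 the two arms also have different lengths in adjacent paragraphs, 20 weeks for A and 16 for B.

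**Working it through.** **Inputs.** Randomisation (V2) is week 0. Titration is 4 weekly doses of 2.5 mg. The 5 mg period is 12 weeks (3.5, 6.1, Annex 7) or 16 weeks (synopsis, 9.3.2). V4 is week 16 and the follow-up call is week 18 ±7 days (Table 1). Compliance is at least 75% of required doses (8.4). Dosing is assumed to start at week 0, with no dose missed or scaled back.

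**Reproducing the schedule.** Total weeks = titration + weeks at 5 mg. With 12 weeks, 4 + 12 = 16, which is V4. Adding the two weeks of Section 9.3.7 gives 18, which is the call in Table 1. The shorter text therefore reproduces the schedule exactly. With 16 weeks, 4 + 16 = 20, and the call would be due at 20 + 2 = week 22, not week 18.

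**Exposure under each text.**

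| Quantity | 4 + 12 | 4 + 16 | Difference |
|---|---|---|---|
| Weeks of drug, weekly doses | 16 | 20 | +4 (4/16 = 25%) |
| Doses at 5 mg | 12 | 16 | +4 (4/12 = 33%) |
| Total dose | 4 × 2.5 + 12 × 5 = 70 mg | 4 × 2.5 + 16 × 5 = 90 mg | +20 mg (20/70 = 29%) |
| Week of last dose | 15 | 19 | +4 |
| 75% compliance cut-off | 0.75 × 16 = 12 doses | 0.75 × 20 = 15 doses | +3 |

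**Coverage under the 20-week text.** The doses of weeks 16, 17, 18 and 19 fall at or after V4. They therefore follow the last scheduled laboratory tests and ECG, and the return of the ketone meter, which Annex 5 says every participant must have. With treatment ending at week 20, the time left after the call is 20 − 18 = 2 weeks. Across the call's window it is 20 − 19 = 1 to 20 − 17 = 3 weeks.

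**Measurement weeks.** Escalated treatment starts at study week 4. Weeks 4, 8 and 16 of it are study weeks 4 + 4 = 8, 4 + 8 = 12 and 4 + 16 = 20. The first two match V3 and P2. Table 1 has nothing at week 20.

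**The case against.** The best defence is that the operational text already closes dosing at week 16. Drug is last dispensed at V3, unused pens come back at V4, and V4 is headed as the end of the intervention. The per-protocol set in Section 11.4.1 runs from the end of titration to 16 weeks of study, and Section 11.4.4 speaks of a 16-week study. Inclusion criterion 6 asks for at least 16 weeks including up-titration, which is compatible with either total. A site working from Table 1 would have no pens for doses after V4. This stands in part: the practical risk is conflicting instructions, and the documents do not show that an unmonitored dosing period would occur. It does not remove the contradiction.

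A reader might infer more than the text supports:

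- *All four extra weeks follow the last safety contact.* They follow the last on-site visit. The week-18 call includes an AE/SAE assessment, so only about two of the four follow it.
- *No off-drug safety contact would remain.* That holds only if the call stays at week 18. Section 9.3.7 ties it to the end of treatment, which would be about week 22.
- *A pump-setting check at V4 is lost.* V4 lists none; the last one listed is at Phone Visit 2.
- *Loss of the study CGM is a safety gap.* Section 8.10.1 says its values are not for diabetes management.
- *The efficacy comparison is affected.* The primary outcome is read at week 16, over the 12 weeks after escalation, under either text.

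On Section 9.2.2, weeks 4, 8 and 16 would match P1, V3 and V4 if counted from randomisation. The sentence counts from escalation, however, and even on the other reading the set differs from weeks 8, 12 and 16.

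**Conclusion.** The contradiction is real, and it must be resolved because it concerns how long participants take the drug. Current text supports 20 weeks (20 doses, 90 mg) in the synopsis and Section 9.3.2, and 16 weeks (16 doses, 70 mg) in Sections 3.5 and 6.1 and Annex 7. The arm B period, the primary endpoint window, the dispensing and return of drug, and the timing of V4 and the call agree only with 16 weeks in total. Table 1 states no dose duration itself, so its support is inferred from the visit weeks.

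Under the 20-week text, four weekly doses lie beyond the last on-site assessments and about two (one to three across the window) lie beyond the week-18 call. These counts assume a first dose at week 0 and full dosing. The measurement weeks in Section 9.2.2 are a separate, smaller inconsistency. The need to act rests on the conflicting duration alone, and nothing here decides which duration is right.

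**What to change.** Reconcile the synopsis (Study Product / Intervention; Measurements and procedures), the arm A text of Section 9.3.2 and Section 9.2.2 with Sections 3.5 and 6.1, the arm B text of Section 9.3.2, Section 9.3.7, Annex 7 and Table 1. The document should then state one treatment duration, and the visit schedule and follow-up call should agree with it. State the measurement weeks once, with their starting point, and use the same set in Sections 6.1, 9.2.2 and 11.4.3. The sponsor must confirm which duration is intended.

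The cost is a wording amendment with no additional participants. If the confirmed duration runs past the visits now in Table 1, the schedule would have to be amended as well.

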#### Randomization arm B. Standard of Care+AID

Participants in arm B will continue with the SoC for diabetes management and AID during the titration and assessment period (16 weeks).

#### Both randomization arms:

During this visit, the study team will also perform the following evaluations:

- Vital signs (blood pressure, heart rate, and temperature)
- ECG
- Body composition (BIA)
- MAFLD and liver fibrosis assessment (*FibroScan*®)
- Urine pregnancy test
- Device downloads (CGM and pump data)
- Apps Downloads (SNAQ App, activity tracker)
- Questionnaires (DTSQs), the participant will complete a paper questionnaire, and the study staff will enter the data in REDCap.
- The hypoglycemia diary will be collected and reviewed
- AE/SAE assessment according to **Section. 10**

Additionally, all participants will receive the CGM Dexcom G7 system (re-supply), a Ketone meter, and additional supplies (test strips, lancing devices, and lancets).

### 9.3.3 Phone Visit 1

#### Intervention arm:

The study staff will contact the participant to give instructions for escalation to the target dose (5 mg SC weekly). The investigators judge that participants might need more time in the titration phase. This visit can also be used to adjust the insulin pump's parameters if needed (**See Annex 3**).

#### Both randomization arms:

The study staff ensures that the data from the devices (CGM and pump data) have been downloaded, the hypoglycemia diary reviewed, and performs the AE/SAE assessment according to **Section. 10**.

### 9.3.4 Visit 3

#### Both randomization arms:

During this visit, the study team will perform the following evaluations.

- Weight, height, waist & hip circumference, waist-to-hip ratio
- Vital signs (blood pressure and heart rate)
- ECG
- Urine pregnancy test
- Device downloads (CGM and pump data)
- Apps Downloads (SNAQ App, activity tracker)

- AE/SAE assessment according to **Section. 10** (including assessment for clinically significant hypoglycemia, severe hypoglycemia, and DKA)
- The hypoglycemia diary will be collected and reviewed.
- Laboratory tests including total bilirubin, indirect and direct bilirubin, ALT, AST, pancreatic serum amylase, serum lipase, and creatinine with eGFR (calculated by CKD-EPI).

Intervention arm:

The participant's medication logbook will be reviewed, the IMP's used pen will be collected, and the study physician will configure the systems and pump's parameters if needed (**See Annex 3**).

### 9.3.5 Phone Visit 2

Both randomization arms:

During this visit, the study team will contact the participants by phone. The study staff ensures that the data from the devices (CGM and pump data) have been downloaded, the hypoglycemia diary reviewed, and perform the AE/SAE assessment, according to **Section 10**.

Intervention arm:

If needed, the study physician will configure the systems and pump's parameters (**See Annex 3**).

### 9.3.6 Visit 4 – End of intervention

Both randomization arms:

During this visit, the study team will perform the following evaluations:

- Weight, height, waist & hip circumference, waist-to-hip ratio
- Vital signs (blood pressure and heart rate)
- ECG
- Body composition (BIA)
- MAFLD and Liver fibrosis assessment (FibroScan®)
- Urine pregnancy test
- Device downloads (CGM and pump data)
- AE/SAE assessment according to **Section. 10** (including assessment for clinically significant hypoglycemia, severe hypoglycemia, and DKA).
- The hypoglycemia diary will be collected and reviewed.
- Questionnaires (DTSQc), the participant will complete a paper questionnaire, and the study staff will enter the data in REDCap.
- Laboratory tests including total bilirubin, indirect and direct bilirubin, ALT, AST, pancreatic serum amylase, serum lipase, creatinine with eGFR (calculated by CKD-EPI), uACR, calcitonin, HbA1c, CT, LDL, HDL, and triglycerides.

At visit 4, all the study devices will be returned.

Intervention arm:

The participant's medication logbook will be reviewed and collected. As well as the IMP's used pens.

